#### Statistical method for primary and secondary outcomes

The primary analysis will follow the intention-to-treat (ITT) principle. We will assess outcomes at the patient level, accounting for the correlated nature of data within surgeon and hospital by using multilevel mixed-effects models. The primary outcome (30-day mortality) will be presented as a number and proportion for each group. We will incorporate random intercepts for surgeons and units in the multilevel models and adjust for variables related to the site, surgeon characteristics, and type of operation. The odds ratio of death for the intervention vs. the control group will be presented with a two-tailed 95% confidence interval (CI) and accompanying *p*-value. The primary null hypothesis of no difference in mortality between the two groups will be rejected if the two-tailed *p*-value is < 0.05.

Binary secondary outcomes (unplanned reoperation and readmission) will be analyzed with the same model approach as used for the primary outcome. For the time-to-event outcome length of stay, we will use a multilevel mixed-effects parametric survival model parameterized as an accelerated failure time model. Random and fixed factors will be used as described above. The results will be presented as the difference in days with 95% CIs. Length of stay will be censored at the time of death or transfer to another hospital. Depending on the number of in-hospital deaths, we will consider a competing risk regression as the primary analysis approach for this outcome. Differences between the groups will be evaluated using multilevel mixed-effects linear regression, adjusting for random and fixed factors as described above. The results will be presented as the mean difference with 95% CI.

We will report results in accordance with the 2010 Consolidated Standards of Reporting Trials (CONSORT) statement extension to cluster-randomized trials [41].

#### Statistical methods for additional analyses

As a secondary analysis, we will perform a per-protocol analysis, excluding operations where the surgeon in the intervention group did not adhere to the protocol and where surgeons in the control group actually performed a StOP?. However, it is now well known that a naïve per-protocol analysis is problematic as it does not properly take confounding/selection bias into account [42]. Direct and indirect adjustment methods are described to estimate the per-protocol effect of a point intervention such as the StOP?-protocol [43]. We will explore the possibility to directly adjust for confounders by using inverse probability weighting [43].

Because cluster randomization may lack the optimal balancing in characteristics between the groups seen in individual-level randomization, we will adjust each model for additional pre-defined patient-level, surgeon-level, and hospital-level variables to account for case-mix differences between the groups in a sensitivity analysis. Moreover, we will qualitatively assess the imbalances of hospital, surgeon, and patient characteristics between the groups. If we observe relevant imbalances in covariates not considered in the primary and sensitivity analyses, we will perform additional adjustments and consider propensity score-based approaches to assess the robustness of our results.

In exploratory analyses, we will assess the adherence and study the influence of the number of StOP?-protocols on outcomes. Such analyses include the assessment of the impact of surgeons’ gender or patients’ gender on primary or secondary endpoints.

We plan exploratory analyses based on the collected data. One such analysis concerns predictors of adherence to the protocol, based on adherence data. We also plan to investigate the changes in outcomes based on surgeon experience with the StOP?-protocol (number of operations with StOP?. Further exploratory analyses will assess the impact of surgeon and patient gender on adherence and on endpoints.

*Interaction between the treatment and the control group*: An important aspect is that surgeons in the control group may be operating together with surgeons in the intervention group within a surgical department. Three different combinations are expected: (i) both surgeons are from the intervention group (25% of interactions), (ii) both surgeons are from the control group (25% of interactions), and (iii) one surgeon is from the intervention group and the other from the control group (50% of interactions). The observations from the StOP? I study showed that collaborations between board-certified surgeons are much more common in university (90% of the procedures) and large teaching (30% of procedures) hospitals, and less frequent in rural hospitals (5% of the procedures). We take this into account for the sample size calculation and the data analyses.

We will conduct exploratory analyses for operations jointly performed by surgeons that are assigned to different treatment groups with a special emphasis on the influence of hierarchical status on adherence to the StOP?-protocol.

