#### Operations

Elective and emergency operations performed by a cluster (surgeon) during the cluster-specific time period will be considered for inclusion. We expect an operation volume of 30 eligible operations per surgeon within 4 months. This number is the target per cluster but the actual number will vary among surgeons.

Exclusion criteria for operations include the following:Patient age below 18 yearsPrevious operation at the same site up to 30 days prior to the index operationProcedures not done in operating rooms but in outpatient clinics, onwards, etc.Mainly diagnostic endoscopic procedures (e.g., colonoscopy, gastroscopy, bronchoscopy)Percutaneous interventions (e.g., transurethral interventions)Documented refusal of the patient for the use of healthcare-related data

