#### Patient and operation characteristics

We will collect data about the type of operation, date of admission, date of operation, time of incision, time of last stich, duration, surgical access, level of urgency, and IDs of the surgeons and residents present during the operation. Patient characteristics include gender, age at the time of operation, height, weight, previous laparotomies at the same site 30 days prior the operation, ASA score, and wound contamination class.

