### Randomization

#### Allocation sequence

Enrolled clusters will be randomized in a 1:1 fashion to either the StOP? or the standard arm. Randomization will be stratified by surgical department and seniority (Chef-/Leitende Ärztin/Arzt versus other).

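### The model that decides the primary mortality hypothesis leaves patient case-mix (age, ASA score and possibly urgency) to a sensitivity analysis, giving up some precision and some protection against differences between arms

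*Protocol article*

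**What the plan says.** Protocol article, Statistical method for primary and secondary outcomes: the mortality model has random intercepts for surgeons and units and will "adjust for variables related to the site, surgeon characteristics, and type of operation". No patient-level variable is named. The null hypothesis is rejected on the two-sided p-value from this analysis. Binary secondary outcomes use the same approach, and length of stay uses the same random and fixed factors.

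Statistical methods for additional analyses: each model is also adjusted for further pre-defined patient-, surgeon- and hospital-level "variables to account for case-mix differences between the groups in a sensitivity analysis". The stated reason is: "Because cluster randomization may lack the optimal balancing in characteristics between the groups seen in individual-level randomization". Covariates in neither model are added only if a relevant imbalance is seen.

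Patient and operation characteristics: "Patient characteristics include gender, age at the time of operation, height, weight, previous laparotomies at the same site 30 days prior the operation, ASA score", together with wound contamination class. Urgency stands in the list of operation data: "duration, surgical access, level of urgency, and IDs of the surgeons and residents present during the operation".

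Operations: "Elective and emergency operations performed by a cluster (surgeon) during the cluster-specific time period will be considered for inclusion".

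Allocation sequence: "Randomization will be stratified by surgical department and seniority". No patient factor is used.

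**The concern.** The protocol gives a reason to adjust for case-mix and then keeps that adjustment out of the analysis that decides the trial. This is a stated placement, not a detail left to the SAP.

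Table 1 places allocation before a surgeon's study operations begin. The trial is open label, and surgeons in one department work closely together. Baseline risk is mixed, because elective and emergency cases from several specialties are eligible. Arms could therefore differ in patient risk by chance, or because cases are distributed differently once allocation is known.

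Two things are at stake: power, if patient factors predict death beyond what type of operation captures, and a clear verdict if the primary and case-mix-adjusted results disagree. In that event the p < 0.05 decision stays with the model that ignores patient risk.

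**Working it through.** **Inputs from the protocol (Sample size calculation).** Control mortality 1.8%; target 0.9% (OR 0.5); 400 clusters, 200 per arm; mean size 24; CV 0.5; ICC 0.024; two-sided 0.05; stated power 84% from a z-test without covariates.

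**1. The protocol's own figure.**
- Design effect = 1 + ((1 + 0.5²) × 24 − 1) × 0.024 = 1.696. Effective n per arm = 4,800 / 1.696 = 2,830.
- Null SE = √(2 × 0.0135 × 0.9865 / 2,830) = 0.003068. Alternative SE = √((0.018 × 0.982 + 0.009 × 0.991) / 2,830) = 0.003066.
- Power = Φ((0.009 − 1.96 × 0.003068) / 0.003066) = Φ(0.974) = 83.5%.
- The relative-efficiency form of the design effect (1.648) gives 84.5%. The stated 84% is reproduced. It uses no covariates, so the sample size does not depend on the choice discussed here.

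**2. Expected deaths.** At an average risk of 1.35%: 9,600 × 0.0135 = 129.6; 12,000 × 0.0135 = 162; 14,000 × 0.0135 = 189.

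**3. Power with and without patient covariates (simulation, 800 trials per row).** Assumptions: total prognostic SD 1.5 or 2.0 on the logit scale; 30% or 50% of its variance already captured by type of operation; between-surgeon case-mix ICC 0.1; surgeon SD 0.284 (latent ICC 0.024); gamma cluster sizes; logistic regression with cluster-robust SEs.

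| Intervention risk | SD | Captured | Primary model | Plus patient covariates | Gain (points) |
|---|---|---|---|---|---|
| 0.9% | 1.5 | 30% | 96.1% | 97.9% | 1.8 |
| 0.9% | 1.5 | 50% | 97.0% | 98.4% | 1.4 |
| 0.9% | 2.0 | 30% | 95.5% | 98.1% | 2.6 |
| 0.9% | 2.0 | 50% | 95.8% | 98.0% | 2.2 |
| 1.08% | 1.5 | 30% | 84.4% | 88.1% | 3.7 |
| 1.08% | 1.5 | 50% | 82.8% | 85.6% | 2.8 |
| 1.08% | 2.0 | 30% | 79.1% | 87.9% | 8.8 |
| 1.08% | 2.0 | 50% | 81.8% | 88.2% | 6.4 |

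The simulated levels should not be set against 84%. They treat the ICC as a latent-scale quantity, which fits its origin in a mixed-effects logistic model, and the protocol's own simulation also exceeds 90%. The differences between columns are what matter.

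**4. How large a chance difference between arms is.** For a covariate with SD 1 and between-surgeon ICC ρ, the SD of the arm difference is √(2 × (1 + 29ρ) / 4,800), where 29 = 1.25 × 24 − 1.
- ρ = 0.1: √(2 × 3.9 / 4,800) = 0.040.
- ρ = 0.2: √(2 × 6.8 / 4,800) = 0.053.

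Simulated values were about 0.04 to 0.055. A 0.1 SD difference is thus 0.1 / 0.053 = 1.9 to 0.1 / 0.040 = 2.5 chance SDs. A 0.2 SD difference is about 3.8 to 5.

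**5. What such a difference does.** With 40% of prognostic variance captured, the uncaptured log-odds SD is 1.5 × √0.6 = 1.16 or 2.0 × √0.6 = 1.55. A 0.1 SD shift multiplies the conditional odds by exp(0.116) = 1.12 or exp(0.155) = 1.17. Simulated with no true effect:
- 0.1 SD: primary OR 1.12–1.13, rejection 11–12%; with patient covariates OR 0.99–1.01, rejection about 5%.
- 0.2 SD: primary OR 1.25–1.32, rejection 29–43%; with patient covariates OR 1.01, rejection about 6%.

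These shifts are imposed in every simulated trial. When imbalance is left to chance, type I error is near nominal in both analyses: 5.9–6.2% without and 5.3–5.4% with the patient covariate.

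**The case against.** The primary model is far from unadjusted. Type of operation, surgeon and site terms absorb part of case-mix, and randomization is stratified by department and seniority. Patient-level adjustment is pre-defined, and an imbalance review follows with possible further adjustment and propensity-score methods. The dispute is only over which pre-specified model carries the p-value. With at most 189 deaths over 400 surgeons (under 0.5 each), two random intercepts and existing fixed effects, a sparse primary model is defensible. The movement of the OR on adding covariates is partly non-collapsibility, a change of estimand and not an error. All of this stands and limits the size of the point, but it gives no reason to prefer the model without patient risk as the decisive one.

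A reader might infer more than the documents support:
- *That urgency is certainly omitted.* The article names categories, not a covariate list, and urgency is listed with the operation data. It may fall under type of operation.
- *That age, ASA score and urgency are the strongest predictors, recorded before incision for every operation.* The protocol states neither. Table 2 shows patient and operation characteristics gathered monthly with outcome data, and gives no completeness figures.
- *That cases are steered by arm.* The open-label design permits it, but nothing in the protocol shows it. Enrolment is consecutive, and all operations of a randomized surgeon in the enrolment period are analysed.
- *That the gain equals about 15% more patients.* That figure comes from a simulation with strong assumed predictors and a conditional OR of 0.55, where power rose from 85% to 90%. It is not the design effect, and the 85% is not comparable with the protocol's 84%.

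**Conclusion.** The point holds as a worthwhile improvement. It is not a validity failure, and it would be wrong to call the planned test biased: chance imbalance leaves type I error about nominal. The cost of the present placement is a small power loss at the design effect, a larger one if the true effect is weaker, and exposure of the decisive estimate to an unlucky or systematic arm difference in patient risk.

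Every size given rests on assumed predictor strength and between-surgeon case-mix variation, which the documents do not report. The simulations also used cluster-robust logistic regression instead of the planned random-intercept model, and did not model department stratification. The 0.2 SD results matter only if case assignment differs systematically by arm, since chance would hardly produce them.

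**What to change.** Name age, ASA score and urgency (unless type of operation already covers it) as fixed effects in the primary mortality model, using values established before the operation. Do the same in the models for reoperation, readmission and length of stay. Keep the present model, without patient covariates, as the sensitivity analysis. State that the reported OR is conditional on these covariates; in the simulations at the design effect it moved from 0.49 to between 0.45 and 0.47.

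The cost is a wording change in both protocol and SAP, because the protocol itself fixes the placement. It should be made before outcomes are seen by arm, hence before the futility analysis at 200 clusters. The planned imputation covers missing outcomes and would have to extend to missing covariates. About 130–190 expected deaths should support a few extra terms. The sample size is unaffected.

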#### Analysis of population and missing data

The main analysis will be based on the intention-to-treat analysis set where all operations of a randomized surgeon done during the enrolment period are analyzed in the randomized arm, regardless of adherence. The per-protocol analysis set consists of all operations where the surgeon was adherent, i.e., if a surgeon in the control group performs a StOP?-protocol during an operation, such operations will be excluded and, if a surgeon in the intervention group does not perform a StOP?-protocol, such operations will be excluded.

We do expect only few missing data with respect to the primary outcome (30-day mortality). We will impute missing outcome data based on all available baseline characteristics of hospitals, surgeons, and patients using chained equations. Analyses will be conducted as described above using Rubin’s rules to combine measures across multiple data sets [44]. This will be done for the analyses of the primary endpoint and the three key secondary endpoints.

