#### Endpoints

The primary endpoint is death up to 30 days after the start of the index operation. This information will be provided by the hospital. The hospital obtains the information from patient records and, if not available, via the patients directly, the family, or the general practitioner.

The following secondary endpoints will be assessed:Unplanned reoperation within 30 days is defined as any operation after the end of the index operation for up to 30 days. Only reoperations within the same hospital of the index operation will be considered. The definition of type IIIb (surgical reoperation) of the Clavien-Dindo Classification will be used to define this variable [40]. Data will be obtained from medical records.Length of index hospital stay is defined as days between the index operation to discharge or transfer to another hospital. In-hospital deaths will be recorded and considered as censoring events. Data will be obtained from medical records.Unplanned readmission within 30 days is defined as any unplanned readmission at the same hospital as the index hospital within 30 days after the operation. Readmissions that are mentioned already in the discharge letter of the index hospital stay are considered planned if the reason for the readmission matches to the one described in the discharge letter. Data will be obtained from medical records.We plan to conduct additional analyses on surgical site infections as an endpoint. Data on surgical site infections are collected according to international standards defined by the Centers for Disease Control and Prevention (CDC) by the surveillance system of Swissnoso—the national center for the prevention of infections in Switzerland. Type 1 (superficial), type 2 (fascial), and type 3 (organ/space) infections are distinguished (91). Swissnoso collects data only in Switzerland and only for a subset of operations. The data will be obtained from Swissnoso and form a pragmatic subsample of data that is available.

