### Withdrawal and discontinuation

Based on the previous study (StOP? I) [31], retention problems with regard to surgeons and patients are likely to be very low. This assumption is justified by the relatively short enrollment period per surgeon and the short follow-up for the primary endpoint. Even if patients drop out, ascertaining whether patients are alive at 30 days is often still possible. With regard to patient retention, the biggest risk is that patients do not give or withdraw consent to use their data which we deem unlikely given the low patient burden.

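### Missing 30-day mortality is to be imputed from baseline characteristics, although almost all patients concerned are known to have left hospital alive

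*Protocol article*

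**What the plan says.** The section Analysis of population and missing data names the basis of the imputation: "We will impute missing outcome data based on all available baseline characteristics of hospitals, surgeons, and patients using chained equations". Results are then pooled with Rubin's rules. On scope it adds: "This will be done for the analyses of the primary endpoint and the three key secondary endpoints". It expects few missing values for the primary outcome but gives no figure.

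The Endpoints section describes how vital status is obtained: "The hospital obtains the information from patient records and, if not available, via the patients directly, the family, or the general practitioner". For length of stay, discharge and transfer are taken from the medical records, and "In-hospital deaths will be recorded and considered as censoring events". Reoperation and readmission at the index hospital also come from the records. Withdrawal and discontinuation adds: "Even if patients drop out, ascertaining whether patients are alive at 30 days is often still possible".

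**The concern.** Because death in the index hospital is recorded, a patient whose 30-day status is unknown is almost always one who was discharged or transferred alive before day 30. For that patient the trial already holds the most informative facts: alive on a known date, and whether a same-hospital reoperation or readmission followed. None of these is a baseline characteristic.

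A model fitted to all patients on baseline variables estimates the risk of dying from the start of the operation to day 30. The patient with missing status has already survived part of that interval, usually the part with the highest risk. Imputed deaths are then too many in both arms. At stake are the reported mortality proportions and, if one arm has more missing outcomes than the other, the odds ratio of the primary analysis.

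**Working it through.** **Inputs from the Sample size calculation section.** Control mortality 1.8%, intervention mortality 0.9%, at least 12,000 patients, hence 6,000 per arm and 108 + 54 = 162 expected deaths.

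**The plan's own figure.** The plan gives no figure for missing data. As a check on the inputs, its 84% power was reproduced:
- Design effect = 1 + ((0.5² + 1) × 24 − 1) × 0.024 = 1.696.
- Effective size per arm = 200 × 24 / 1.696 = 2,830, which gives 83.5% power for 1.8% against 0.9%.
- An alternative design effect for unequal cluster sizes (1.648) gives 84.5%.

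**Assumptions, not in the document.** The missing fraction M is 0.5% to 5%. The share q of 30-day deaths that occur after leaving hospital is 10% to 50%. All patients with missing status left hospital alive, and within that group missingness is unrelated to death.

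**Step 1. Risk given that the patient left alive.** With p the 30-day risk, r = qp / (1 − (1 − q)p). In the control arm:
- q = 10%: 0.0018 / 0.9838 = 0.18%
- q = 50%: 0.009 / 0.991 = 0.91%

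Against an average of 1.8% these are ratios of about 10 and 2.

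**Step 2. Average risk that baseline imputation assigns.** This is the risk among patients with known status: p_obs = [(1 − q)p + (1 − (1 − q)p − M) r] / (1 − M). It is also the arm's estimated risk after imputation.

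**Step 3. Imputed control-arm deaths.** These are 6,000 × M × p_obs, compared with 6,000 × M × r.

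| M | Patients missing | Baseline basis | Given left alive (q = 10% to 50%) | Surplus |
|---|---|---|---|---|
| 1% | 60 | about 1.1 | 0.1 to 0.5 | about 0.5 to 1 |
| 5% | 300 | 5.5 to 5.7 | 0.5 to 2.7 | about 3 to 5 |

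**Step 4. Odds ratio, equal missingness, arm in the model.** The true value is (0.009/0.991) / (0.018/0.982) = 0.4955. With M = 5% and q = 10% the estimated risks become 1.89% and 0.94%, and the odds ratio is 0.4953. It stays at 0.495 across the whole grid, because both risks are inflated by nearly the same factor.

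**Step 5. Odds ratio, unequal missingness.** Take 5% missing in the intervention arm, none in the control arm, and q = 10%:
- r = 0.0009 / 0.9919 = 0.000907
- p_obs = (0.0081 + 0.9419 × 0.000907) / 0.95 = 0.00943
- OR = (0.00943/0.99057) / (0.018/0.982) = 0.519

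With the 5% in the control arm instead, the odds ratio is 0.473. Other values of q fall between these two. A 2-point difference gives 0.486 to 0.505. With no true effect (1.8% in both arms), a 5-point difference gives 0.954 to 1.048.

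**The case against.** The text does not say that baseline characteristics are the sole predictors. Chained equations run over four endpoints commonly let each endpoint inform the others, so length of stay, reoperation and readmission may enter in any case. The imputation also conditions on patient data such as age, ASA score and urgency, so a low-risk patient is imputed at low risk; 1.8% is an average, not a value given to everyone. Few outcomes are expected to be missing, and the missing fraction and post-discharge share used above are assumptions. Transferred patients may be at higher risk than those sent home, which would narrow the gap. Follow-up is centralised and done by blinded personnel, so a large difference in missingness between arms is not the likeliest case. The secondary endpoints come from the index hospital's own records, so little should be missing there.

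Most of this stands and limits the size of the point. It does not remove it. The article names a predictor set, and being alive at discharge on a known date is not in it. Conditioning on baseline does not help either: within any stratum of age, ASA score and urgency, the fitted risk still includes the in-hospital deaths.

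Two stronger readings are tempting and are not supported. A reader might infer that trial arm is left out of the imputation, which would move the odds ratio to between 0.497 (0.5% missing) and 0.514 (5% missing) even with equal missingness. But the section Participating surgeons lists study arm among the surgeon data, and the imputation uses all available surgeon characteristics. A reader might also infer that clustering is ignored, because the analysis is described as "accounting for the correlated nature of data within surgeon and hospital by using multilevel mixed-effects models" and the imputation paragraph mentions no random effects. That paragraph is silent on the matter, and a statistical analysis plan may settle it.

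**Conclusion.** The point holds as a cheap improvement of small size. Followed as written, the imputation gives patients known to have left hospital alive a risk roughly 2 to 10 times too high. The surplus in the control arm is about 0.5 to 1 deaths at 1% missing and about 3 to 5 at 5% missing, beside 108 expected there. The odds ratio is essentially unaffected when missingness is equal between arms. It moves to between 0.473 and 0.519, against 0.4955, only with a 5-point difference between arms. All of these sizes rest on the assumed missing fractions, the assumed 10% to 50% post-discharge share of deaths, and all missing cases having left hospital alive. The documents do not support a claim that the primary comparison is seriously biased.

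**What to change.** Extend the stated imputation basis beyond baseline characteristics to discharge or transfer status and date (the last date known alive), length of stay, reoperation and readmission. Confirm in the same sentence that trial arm is in the model. State that death is imputed only for the interval after the patient was last known alive, for example by fitting the mortality imputation among patients who left hospital alive.

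Everything needed is already collected, so the cost is a sentence in the analysis plan and a slightly more complex imputation model. That model should be kept sparing: under the assumed range only about 16 to 81 of the 162 expected deaths (10% to 50%) would occur after discharge.
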